### **10.2 Adverse Event Documentation**

Recording of AEs will begin after the ICD is signed by the subject or subject/parent/LAR. Any medical event occurring before the first dose of the vaccine will be regarded as a pre-treatment administration event. All events occurring after the first dose and prior events that worsen any time after the first dose will be regarded as Treatment Emergent Adverse Events (TEAE).

Any AE occurring after providing the informed consent and until the last study visit will be recorded on the CRF. All TEAEs occurring during the study period will be followed up by the investigator until resolution or stabilization of the event or until the subject is lost to follow-up. This follow-up should be documented in the subject medical records and may be extended beyond the end of the study period.

An **Adverse Event (AE)** is defined as any untoward medical occurrence (including a symptom/disease or an abnormal laboratory finding) in a patient or clinical investigation subject administered a pharmaceutical product at any dose that does not necessarily have to have a causal relationship with this treatment. An adverse event can, therefore be any unfavorable and

unintended sign (including an abnormal laboratory finding, for example), symptom, or disease temporally associated with the use of an investigational product, whether or not considered related to the investigational product. This definition includes inter-current illnesses or injuries and exacerbation of pre-existing conditions.

**Adverse Event Following Immunization (AEFI):** This is defined as any untoward medical occurrence which follows immunization and which does not necessarily have a causal relationship with the use of the vaccine. The adverse event may be any unfavorable or unintended sign, an abnormal laboratory finding, a symptom or a disease.

The adverse events reported and as observed by the investigator will be filled in the case report form and maintained for the purpose of documentation.

The investigator must report adverse events which are clinically apparent, or in the investigator's opinion clinically significant, in the relevant part of the case report form.

**Systemic Reactions (Protocol specific)**

- All reaction during the study will be inquired & recorded for up to 30 minutes on the day of each vaccination and for 3 days post-vaccination. Systemic reactions (fever, Headache, acute allergic reaction, Loss of Appetite, fatigue, vomiting and diarrhea) will be recorded.
- Solicited reactions will be graded as follows.

| General reaction | Mild (Grade 1)                                    | Moderate (Grade 2)                                                                 | Severe (Grade 3)                                                   | Potentially Life Threatening (Grade 4)     |
|-------------------------|----------------------------------------------------------|-------------------------------------------------------------------------------------------|---------------------------------------------------------------------------|---------------------------------------------------|
| Fever                   | 38.0-38.4°C                                              | 38.5-38.9°C                                                                               | 39 – 40                                                                   | > 40.0°C                                          |
| Headache                | No interference with activity                            | Repeated use of non- narcotic pain reliever > 24 hours or some interference with activity | Significant; any use of narcotic pain reliever or prevents daily activity | Emergency room (ER) visit or hospitalization      |
| Fatigue                 | No interference with activity                            | Some interference with activity                                                           | Significant; prevents daily activity                                      | ER visit or hospitalization                       |
| Myalgia                 | No interference with activity                            | Some interference with activity                                                           | Significant; prevents daily activity                                      | ER visit or hospitalization                       |
| Vomiting/ Nausea        | No interference with activity or 1 – 2 episodes/24 hours | Some interference with activity or > 2 episodes/24 hours                                  | Prevents daily activity, requires outpatient IV hydration                 | ER visit or hospitalization for hypotensive shock |

| General reaction | Mild (Grade 1)                    | Moderate (Grade 2)              | Severe (Grade 3)                                                          | Potentially Life Threatening (Grade 4) |
|-------------------------|------------------------------------------|----------------------------------------|----------------------------------------------------------------------------------|-----------------------------------------------|
| Diarrhea                | 2 – 3 loose stools or < 400 gms/24 hours | 4 – 5 stools or 400 – 800 gms/24 hours | 6 or more watery stools or > 800gms/24 hours or requires outpatient IV hydration | ER visit or hospitalization                   |

The occurrence of solicited systemic reactions will be noted in subject diary card by the parent/LAR and copied on to relevant section of the CRF pages by the investigator/designee at the subsequent clinic visit. These reactions will be recorded on the “Solicited Systemic Reactions” section of the CRF along with ‘Date of resolution’; if they do not resolve satisfactorily by 3 days following study immunization.

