|                           | At both follow up telephonic visits after vaccination, the appointed field officer will contact subjects via telephone for 3 consecutive days after the dosing of the vaccine. For safety assessment, the subjects and/or parents/legally acceptable representatives will be instructed to record on the subject diaries adverse events that occur after investigational product dosing.                                                                                                                                                                                                                                                                                                                                                                                                                                                                                                                                                                                                                                                                                                                                                                                                                                                                                                           |

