### 4.5 Adverse Effects

The following adverse events are known to occur with Shanchol use. Acute Gastroenteritis, Diarrhea, Fever, Vomiting, Abdominal pain, Itching, Rash, Nausea, Weakness, Cough, Vertigo, Dryness of mouth, Oral ulcer (rare), Sore throat (rare) and Yellowing of urine (rare). It has been observed that the incidence of adverse events is less after the second dose as compared to the first Special Warnings and Precautions.

The following adverse events are known to occur with Euvichol-Plus. Where, 2,999 healthy children and adults (1-40 years) were participated in the clinical study for evaluating the safety.

1. After taking the vaccines, during first 7 days, the most frequently reported adverse drug reactions in the clinical trial were headache, fever, diarrhea, Nausea/Vomiting and Myalgia and 102 subjects (3.40%) among 2,999 subjects were reported.
2. After taking the vaccines, adverse drug reactions were examined for a period of 28 days. 69 subjects (2.30%) among 2,999 subjects were reported with the adverse effects, and Gastrointestinal disorders were reported the highest numbers i.e., 35 subjects (1.17%). The adverse drug reactions during the study (28 days) were as follows,

| System Organ Class                                     | Uncommon                              | Rare                                        |
|--------------------------------------------------------|---------------------------------------|---------------------------------------------|
| Gastrointestinal disorders                             | Abdominal pain,
Toothache Diarrhea | Vomiting, Upper
abdominal pain           |
| General disorders and
administration site condition | Pyrexia                               | Thirst                                      |
| Infection and infestations                             | Nasopharyngitis                       | Gastroenteritis                             |
| Nervous system disorders                               | Headache                              | Dizziness                                   |
| Respiratory, thoracic and
meditational disorders    | Cough                                 | Oropharyngeal pain                          |
| Skin and subcutaneous tissue
disorders              | Pruritus                              | Rash macular                                |

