### **7.2 Exclusion Criteria:**

Any one of the following

1. History of cholera vaccinations or history of cholera.
2. History of hypersensitivity reactions to other preventative vaccinations.
3. Immune function disorders including immunodeficiency diseases.
4. 38°C or higher body temperature measured prior to investigational product dosing.
5. Diarrhea or abdominal pain lasting 2 weeks or longer within 6 months prior to study initiation. Also, administration of antidiarrheal drugs or antibiotics to treat diarrhea within 1 week prior to study initiation.
6. Abdominal pain, nausea, vomiting, or decreased appetite within 24 hours prior to study initiation.
7. Pregnant or lactating women.
8. Children vaccination within 1 month prior to study initiation or planned vaccination during the study.
9. Participation in another clinical trial with investigational product dosing within 6 months prior to study initiation.
10. An individual thought to have difficulty in participating in the study due to severe chronic diseases, based on the judgment of the investigator.

11. An individual thought to have difficulty participating in the study due to other reasons, based on the judgment of the investigator.
12. If female patient will get pregnant after first vaccination

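### Section 10.2 gives two different sets of terms for the solicited-reaction endpoint, and abdominal pain is in neither

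*Supplement*

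**What the plan says.** Solicited adverse events on Day 0 to 3 are a named safety endpoint (section 3.0, Endpoints; section 4.8). Comparing safety between the two vaccines is the only secondary objective (section 4.7).

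Under Systemic Reactions in section 10.2, the protocol lists the reactions to be recorded: "fever, Headache, acute allergic reaction, Loss of Appetite, fatigue, vomiting and diarrhea". Directly below is a table that grades the solicited reactions from 1 to 4. Its rows are fever, headache, fatigue, myalgia, vomiting/nausea and diarrhea. The text then turns to the diary: "The occurrence of solicited systemic reactions will be noted in subject diary card by the parent/LAR". From there, solicited reactions go to their own section of the CRF.

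An event is unsolicited if it does not meet what the diary prelists, and it then goes to the CRF's adverse event pages (section 10.2, Unsolicited Adverse Events). The diary card is not among the documents.

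Section 4.5 gives the known reactions. For Shanchol they begin "Acute Gastroenteritis, Diarrhea, Fever, Vomiting, Abdominal pain, Itching, Rash, Nausea, Weakness". For Euvichol-Plus over the first 7 days, "the most frequently reported adverse drug reactions in the clinical trial were headache, fever, diarrhea, Nausea/Vomiting and Myalgia". The 28-day table for Euvichol-Plus has abdominal pain as uncommon and upper abdominal pain as rare.

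**The concern.** An endpoint made up of named symptoms needs one list of members. Section 10.2 offers two, and neither contains the other. Whoever builds the diary and CRF must choose between them. A diary built from the list would not prompt for myalgia or nausea. One built from the table would not prompt for loss of appetite or acute allergic reaction. Because solicited and unsolicited events go to different CRF pages, the choice decides which safety table a symptom appears in. If the eight centers read section 10.2 differently, that could also vary by site.

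The second part is the absence of abdominal pain. Both vaccines are oral, and exclusion criterion 6 already screens for it before dosing, next to the symptoms that are followed afterwards: "Abdominal pain, nausea, vomiting, or decreased appetite within 24 hours prior to study initiation".

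At stake is how clear and complete the descriptive safety comparison is, including the adult 14-day data that the DSMB reviews before children are enrolled (section 11.0). Immunogenicity is not affected.

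**Working it through.** The plan gives no figure to reproduce here. The check compares terms.

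| Term | 10.2 list | 10.2 grading table | 4.5 Shanchol | 4.5 Euvichol-Plus |
|---|---|---|---|---|
| Fever | yes | yes | yes | yes, first 7 days |
| Headache | yes | yes | no | yes, first 7 days |
| Fatigue | yes | yes | weakness only | no |
| Vomiting | yes | yes | yes | yes, first 7 days |
| Diarrhea | yes | yes | yes | yes, first 7 days |
| Acute allergic reaction | yes | no | not by that name | not by that name |
| Loss of appetite | yes | no | no | no |
| Myalgia | no | yes | no | yes, first 7 days |
| Nausea | no | yes (row shared with vomiting) | yes | yes, first 7 days (joined with vomiting) |
| Abdominal pain | no | no | yes | yes, 28 days (uncommon) |

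**Count.** The list has 7 terms. The table has 7 terms in 6 rows. They share 5, so 7 − 5 = 2 terms are only in the list and 7 − 5 = 2 only in the table, a difference of 4 terms. Counted by rows, nausea is absorbed into the vomiting row and the difference is 3. The union is 5 + 2 + 2 = 9 terms, without abdominal pain.

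**Gastrointestinal symptoms.** Section 4.5 names four for both vaccines: diarrhea, vomiting, nausea and abdominal pain. Three are in the list or the table; abdominal pain is in neither. Loss of appetite is in the list, although section 4.5 names it for neither vaccine.

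**What the documents give on size.** All of it comes from the Euvichol-Plus record in section 4.5 (2,999 subjects aged 1 to 40, drug reactions only).

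- Gastrointestinal disorders over 28 days: 35/2,999 = 1.17%. Applied to an arm of 208: 0.0117 × 208 = 2.4 subjects.
- Most frequent reactions, first 7 days: 102/2,999 = 3.40%. Applied to 208: 0.0340 × 208 = 7.1 subjects.
- All reactions over 28 days: 69/2,999 = 2.30%.

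None of these is a rate for abdominal pain, myalgia or nausea alone. The 7-day count (102) exceeds the 28-day count (69), so one record is not nested in the other and a Day 0 to 3 share cannot be derived.

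**Precision, as illustration.** Assume the same rate p in both arms of 208. The approximate 95% half-width for a difference is 1.96 × √(2p(1 − p)/208). At p = 1.17% this is 1.96 × √(2 × 0.0117 × 0.9883/208) = 2.1 percentage points. At p = 3.40% it is 1.96 × √(2 × 0.0340 × 0.9660/208) = 3.5 percentage points. At rates like these the comparison is descriptive.

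**The case against.** The strongest reply is that the diary card decides what is solicited, and it is not shown. It may already print abdominal pain, myalgia and nausea. That stands, and it makes the abdominal pain point conditional. It does not remove the disagreement between list and table, which lies within section 10.2. One might also say that the list is headed systemic reactions and only the table solicited reactions. But both stand under one heading, and the diary sentence that follows speaks of solicited systemic reactions as a single set.

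Second, nothing obliges a protocol to solicit every known reaction. Cough, itching and rash are not in either set by name. The grading table covers every reaction named as most frequent in the first 7 days, and abdominal pain is not among them. This is fair, and it makes adding abdominal pain a recommendation and not the correction of an error. The case for it is that it is the only gastrointestinal symptom named for both oral vaccines that is left out.

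Three stronger readings are tempting, and the documents do not support them.

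- *Abdominal pain would be missed, or would bias the comparison.* The protocol says "All reaction during the study will be inquired & recorded for up to 30 minutes on the day of each vaccination" and for 3 days afterwards. Also, "the appointed field officer will contact subjects via telephone for 3 consecutive days after the dosing of the vaccine", subjects are told to record adverse events in the diary, and section 10.1 has an open question. Unsolicited events run to Day 28 with severity and causality. What may be missing is a prompt by name and the four-grade scale.
- *Loss of appetite and acute allergic reaction cannot be graded.* Section 10.3 requires severity for all solicited reactions and defines mild, moderate and severe, so both can be graded. They only lack four-grade rows.
- *At most 2.4 cases of abdominal pain per arm are at issue.* The 35/2,999 counts drug reactions to Euvichol-Plus at ages 1 to 40. This trial records adverse events regardless of cause, enrolls to age 60, and has a Shanchol arm for which section 4.5 gives no rate. The figure is not an upper limit.

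**Conclusion.** The point holds as a minor one. Section 10.2 states two sets of terms for one named endpoint, four terms apart (three by rows). The two terms missing from the list, myalgia and nausea, are among the most frequent early reactions to the test vaccine. This part rests on the protocol text alone.

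That abdominal pain lacks a prompt by name rests on the assumption that the diary card does not print it. If so, it is still recorded, as an unsolicited event.

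The gain from a correction is small, and its size cannot be derived: the documents give no Day 0 to 3 rate for any single term, and nothing on how many reports a named prompt would add. No event is lost to the endpoints, no bias between arms is claimed, and no immunogenicity conclusion changes.

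**What to change.** Use one set of terms in the section 10.2 list, the grading table, the diary card and the solicited section of the CRF.

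- Add myalgia and nausea to the list.
- Add abdominal pain to the list, table, diary card and CRF, with the four grades already used for fatigue and myalgia.
- For loss of appetite and acute allergic reaction, either add four-grade rows or state that the section 10.3 severity scale applies.

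The cost is wording in section 10.2, up to a few rows in the table and CRF, and a slightly longer diary for subjects and parents. No extra visit, sample or subject is needed. If the diary card and CRF already carry the full set, only section 10.2 changes.

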#### Unsolicited Adverse Events

An unsolicited adverse event is an observed adverse event that follows immunization but does not fulfill the conditions prelisted in the patient diary in terms of symptom/sign and/or timing of onset post-vaccination. All such events will be recorded in the ‘Adverse event’ pages in the CRF.

### **10.3 Severity and Relation of Adverse Event**

All solicited systemic reactions and unsolicited adverse events observed or reported/volunteered by subject/parent/LAR must be recorded in the CRFs with information about severity (i.e., whether mild, moderate, severe) and possible relation to the study vaccine.

**Mild**: usually transient in nature and generally not interfering with normal activities

**Moderate**: sufficiently discomforting to interfere with normal activities

**Severe**: prevents normal activities

**Relationship of AE to study medication will be described as:**

#### **1. Case with adequate information for causality conclusion**

A case with adequate information for causality conclusion can be classified as follows:

##### **A. Consistent causal association to immunization**

- A1.** Vaccine product-related reaction; or
- A2.** Vaccine quality defect-related reaction; or
- A3.** Immunization error-related reaction; or
- A4.** Immunization anxiety-related reaction.

##### **B. Indeterminate**

**B1.** Temporal relationship is consistent but there is insufficient definitive evidence that vaccine caused the event (it may be a new vaccine-linked event). This is a potential signal and needs to be considered for further investigation.

**B2. Reviewing factors result in conflicting trends of consistency and inconsistency**

With causal association to immunization (i.e. it may be vaccine-associated as well as coincidental and it is not possible clearly to favor one or the other).

- C. Inconsistent causal association to immunization (coincidental):** This could be due to underlying or emerging condition(s) or conditions caused by exposure to something other than vaccine.

**2. Case without adequate information for causality conclusion**

This case is categorized as “unclassifiable” and requires additional information for further review of causality. The available information on unclassifiable cases should be placed in source document which should be periodically reviewed to see if additional information is available for classification.

The case should be classified and the classification documented in CRF if this information is available during the AE follow-up period as defined in section 13.2.

Factors that would assist in determining the Causality include:

1. Timing of occurrence of the adverse event
2. Absence of symptoms related to the event prior to exposure
3. Consistency of the event with the established pharmacological/toxicological effects of the product
4. Consistency of the event with the known effects of other products in the class
5. Supporting evidence from other studies or absence of alternative explanations

The serious adverse drug reaction will be recorded in the Serious Adverse Event Reporting form provided separately.

**10.4 Serious Adverse Events Reporting**

Investigator shall report all serious and unexpected adverse events, to the Licensing Authority, the Sponsor, and the Ethics Committee that accorded approval to the study protocol, within 24 hours of their occurrence as per Table 5 of the New Clinical Trial rules March 2019 by telephone/ facsimile/e-mail. The report of the serious adverse event of death, after due analysis shall be forwarded by the Investigator to Chairman of the Ethics Committee and Chairman of the Expert Committee constituted by the Licensing

Authority under Table 5 of the New Clinical Trial rules March 2019 with a copy of the report to the Licensing Authority and the head of the Institution where the trial has been conducted within 14 days of the knowledge of occurrence of SAE death. The report of the serious adverse event other than death, after due analysis shall be forwarded to the Licensing Authority, Chairman of the Ethics Committee and the head of the Institution where the trial has been conducted within 14 days of the reporting of serious adverse event.

For the purpose of this technical protocol, a serious adverse event is defined as any unfavorable medical occurrence that

- Results in the death of the participant,
- Is life-threatening,

Note: The term “life-threatening” refers to an event in which the patient was at risk of death at the time of the event; it does not refer to an event, which hypothetically might have caused death if it were more severe.

- Requires inpatient hospitalization or prolongation of existing hospitalization.
- Results in persistent or significant disability or incapacity,

